### Setting and participants

This study will be conducted on couples referring for compulsory pre-marriage training in public health centers in five metropolitan cities of Iran with a diverse geographical distribution (Tehran, Mashhad, Ahvaz, Tabriz and Shiraz) to enhance the generalizability of the findings. We plan to recruit new couples (both men and women) referring for compulsory premarital counselling.

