#### Demographic characteristics questionnaire

Participants will complete the socio-demographic characteristics form including age, education level, income, occupation, ethnicity, gender and geographic area (province and city).

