#### Cardiff fertility knowledge scale (CFKS)

The Persian version of the Cardiff Fertility Knowledge Scale (CFKS) will be used to assess the fertility knowledge. The CFKS consists of 13 items measuring knowledge about facts, risks and myths of fertility. Participants will respond to all items as true, false or do not know. A correct answer is assigned one point and an incorrect or ‘do not know’ answer is assigned zero point. Scores are reported as the percent correct score (0–100%). The Cronbach’s alpha coefficient of the CFKS was 0.79 and satisfactory for most countries [13].

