### Sample size

According to our primary outcomes including fertility knowledge and intention toward childbearing that are important to be measured 3 months after the intervention, we considered a small standardized Cohen effect size (d = 0.2) with a type I error of 5% (α = 0.05) and a type II error of 10% (β = 0.1; power = 90%) and sample size obtained 527 in each group and considering 15% of loss to follow up, the sample size was calculated 620 couples in each group using the G-Power software. Considering the design effect equals to 1.5, final size was calculated 1240 couples in total (620 couples in each group). In each city around 200 couples (100 in each group) and from Tehran about 440 couples (220 in each group) will be recruited.

It should be noted that in order to compare quantitative outcomes between groups over time (baseline, 3, 12 and 18 month), the sample size obtained 660 couples in total (330 in each group) based on repeated measures ANOVA. So, the initial obtained sample size (620 couples in each group) will have the appropriate power for this analysis.

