### Randomization

Samples will be selected through stratified sampling and random samples are then selected from each stratum. The strata consist of five cities, and separate randomization lists will be prepared for each city using a block randomization.

Due to the limited number of main public centers providing compulsory premarital counselling in each city (3 centers in Tehran, 2 centers in in Ahvaz, 1 center in Shiraz, 2 centers in Tabriz and 3 centers in Mashhad), and other concerns such as selection bias, and generalizability (according to potential confounder of socioeconomic status), the cluster randomization based on the centers is not possible. So, we will use central randomization that is stratified to the cities.

The PI will randomly assign the couples into two groups in each city by a computer-generated random sequence. For randomization, the permuted block randomization will be used (block size = 4). According to the sample size of 440 identified, 110 blocks will be produced using the online site (www.sealedenvelope. com) for Tehran. According to the sample size of 200 identified, 50 blocks will be produced using the online site (www.sealedenvelope. com) for other cities.

Allocation will be concealed by using sequentially numbered opaque sealed envelopes that contain group assignments determined by computer-generated random sequences.

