### Statistical method

Categorical variables will be presented by frequency (%), and quantitative variables will be reported as means (SD) or medians (with 25th to 75th quartiles), as appropriate. Graphical approach, numerical indices and the Shapiro-Wilk test will be used to evaluate the normality distribution and Leven test for homogeneity of variances in quantitative variables, respectively.

Comparisons between groups at baseline will be performed using Chi-square or Fisher-exact test for categorical variables, Independent samples t-test for normally distributed quantitative variables and Mann–Whitney U test for non-normally distributed quantitative variables. To compare the outcomes between the two groups over the time, repeated measures ANOVA will be used. Data will be analyzed using the SPSS software version 22 (IBM Corp. IBM SPSS Statistics for Windows, Armonk, NY, USA). For all analyses, a *P* value < 0·05 will be considered statistically significant.

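### Couples are randomised and both partners are scored, but the only outcome method named (repeated measures ANOVA) has no place for correlation between partners, and no unit of analysis is stated

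*Protocol article*

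**What the plan says.** Under Setting and participants: "We plan to recruit new couples (both men and women) referring for compulsory premarital counselling". Under Randomization: "The PI will randomly assign the couples into two groups in each city by a computer-generated random sequence". The couple is therefore the randomised unit, and both partners are always in the same arm.

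The instruments are completed by individuals. The demographic form includes gender: "Participants will complete the socio-demographic characteristics form including age, education level, income, occupation, ethnicity, gender and geographic area (province and city". For the 13-item knowledge scale, "Participants will respond to all items as true, false or do not know", and each respondent receives a percent-correct score. The intention questionnaire likewise asks for a person's own plans and views. Two respondents per couple are clearly implied, and no score for the couple is defined.

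Under Statistical method, the outcome analysis is a single sentence: "To compare the outcomes between the two groups over the time, repeated measures ANOVA will be used". That section assigns the chi-square, Fisher, t and Mann–Whitney tests to the comparison of groups at baseline.

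The Sample size section starts from an effect size ("we considered a small standardized Cohen effect size (d = 0.2"), counts its results in couples and mentions clustering once: "Considering the design effect equals to 1.5". It does not say what that design effect is for.

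**The concern.** A repeated measures ANOVA of arm by time takes subjects as independent and models the correlation among one subject's four measurements. When couples are randomised, the two partners share an arm, the same teaching and, soon after enrolment, a home. Their scores are likely to be positively correlated. If each person is entered as a subject, the analysis counts twice as many independent units as were randomised, and the variance of the arm difference is understated.

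Knowledge and intention are two of the three primary outcomes, and the Discussion expects the results to inform government policy. A false-positive rate above the stated 5% on those two outcomes would matter. The protocol also leaves open whether the analysed unit is the couple counted in the sample size.

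**Working it through.** **1. The protocol's own figures.** Inputs from Sample size: d = 0.2, alpha 5% (taken as two-sided), power 90%, loss 15%.

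- Two-sample t-test: 526.3, rounded up to 527 per group, as stated.
- Loss to follow-up: 527 / 0.85 = 620 per group, as stated.
- Repeated measures ANOVA: with f = 0.1, four measurements and an assumed correlation over time of 0.5, a total of 660 gives 90.06% power, matching the stated 660.
- Design effect: 527 × 1.5 / 0.85 = 930 per group. The stated 620 is reached without the 1.5, so that factor is not visible in the final number or in the analysis.

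**2. Size of the error if partners are entered as separate subjects.** Let m be couples per arm and ρ the correlation between partners in the quantity tested.

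- True variance of an arm mean: σ²(1 + ρ) / (2m).
- Variance assumed when pairing is ignored: σ² / (2m).
- Assumed SE / true SE = 1 / √(1 + ρ).
- True size of a two-sided 5% test = 2 × [1 − Φ(1.96 / √(1 + ρ))].

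| Assumed ICC | 1 + ICC | SE understated by | 1.96 / √(1 + ICC) | True size |
|---|---|---|---|---|
| 0 | 1.0 | 0% | 1.960 | 5.0% |
| 0.2 | 1.2 | 9% | 1.789 | 7.4% |
| 0.3 | 1.3 | 12% | 1.719 | 8.6% |
| 0.5 | 1.5 | 18% | 1.600 | 11.0% |

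Over a wider range, the size is 6.2% at ICC 0.1 and 13.3% at ICC 0.7.

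**3. Check on the named method.** Repeated measures ANOVA with individuals as subjects was simulated under no effect: 527 couples per arm, four complete time points, correlation over time 0.5, 3000 runs.

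| Assumed ICC | Arm effect, persons as subjects | Arm-by-time, persons as subjects | Arm effect, couple means |
|---|---|---|---|
| 0 | 4.8% | 4.4% | 4.7% |
| 0.3 | 7.8% | 10.7% | 4.5% |
| 0.5 | 11.6% | 15.6% | 5.6% |

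The arm effect agrees with the formula within simulation error. The arm-by-time test is worse because it has three numerator degrees of freedom. These arm-by-time figures assume that partners' changes over time correlate as strongly as their average scores.

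**4. Power once pairing is modelled.** With 527 analysed couples per arm, the effective number of persons per arm is 2 × 527 / (1 + ICC), and power is Φ(0.2 × √(n/2) − 1.96).

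- ICC 0.3: 1054 / 1.3 = 810.8, power 98.1%.
- ICC 0.5: 1054 / 1.5 = 702.7, power 96.3%.

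Both exceed the planned 90% for d = 0.2 on an individual score at one time point.

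**The case against.** The strongest reply is that the protocol never says partners will be entered as independent rows. Its sample sizes are given in couples, including the 660 for the repeated measures ANOVA, and randomisation is by couple. Read that way, the ANOVA unit is the couple and pairing causes no inflation. Couple means, partner as a within-couple factor, or separate analyses by sex would all be valid. A condensed article may also leave model detail to a fuller document. This stands in part: the inflation is conditional. But the protocol does choose its outcome method, and applied to the only scores it defines, which belong to persons, that method does not respect the randomised unit.

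Three stronger readings are tempting, and the text does not support them.

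- A reader might count the t-test and Mann–Whitney test among the affected outcome analyses. Statistical method confines them to baseline; only the Abstract lists them without that limit. Ignoring pairing in a baseline comparison does not affect the error rate of a primary outcome.
- A reader might take the design effect of 1.5 as an admission of a within-couple ICC of 0.5, since 1 + 0.5 = 1.5 for pairs. The Sample size section does not say what it covers, and clustering by centre or city is equally open.
- A reader might conclude that a pregnancy reported by both partners will be counted twice. That again presumes one row per person, which is not stated.

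Finally, the closed-form sizes are for a single comparison of means. The simulation shows that they do not overstate the effect for the named method.

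**Conclusion.** The point holds in conditional form. Couples are randomised, both partners give individual knowledge and intention scores, and the one named outcome method covers correlation over time within a person but not between partners. The protocol states neither a couple-level score nor the unit of analysis.

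If partners are treated as separate subjects and correlate positively, a nominal 5% test has a true size of about 7.4%, 8.6% or 11.0% at an ICC of 0.2, 0.3 or 0.5. Those ICCs are assumptions, and with no correlation there is no inflation. The documents do not support the unconditional statement that the primary results will have understated standard errors. The issue concerns mainly knowledge and intention, because planned pregnancy is an event of the couple.

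**What to change.** State the unit of analysis in Statistical method. For knowledge and intention, replace the repeated measures ANOVA with a linear mixed model that has couple as the cluster, repeated times within person, and fixed effects for arm, time, arm × time and partner (woman or man). GEE clustered on couple would serve as well.

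Two simpler routes also deal with the pairing: repeated measures analysis of couple means, or separate analyses of women and men. If the sexes are analysed separately, say which result is primary. Analyse pregnancy and miscarriage once per couple, and say how the two partners' reports are combined.

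The cost is a change of analysis wording, a little more analysis work and wider intervals. Compared with ignoring the pairing, intervals widen by √(1 + ICC): about 10%, 14% and 22% at ICC 0.2, 0.3 and 0.5. No additional couples are needed for d = 0.2 on an individual score.

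### Randomisation is stratified by city but the stated outcome analysis names no city term; if city is related to outcome, between-couple comparisons are slightly conservative (minor)

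*Protocol article*

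**What the plan says.** The Randomization section of the protocol article makes city the stratification factor: "The strata consist of five cities, and separate randomization lists will be prepared for each city using a block randomization". It rejects cluster randomisation by centre and concludes: "So, we will use central randomization that is stratified to the cities". Within each list, "the permuted block randomization will be used (block size = 4"). The Sample size section sets 1:1 allocation within city: about 200 couples in each of four cities, and "from Tehran about 440 couples (220 in each group) will be recruited".

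The Statistical method section gives one sentence to the outcome comparison: "To compare the outcomes between the two groups over the time, repeated measures ANOVA will be used". The Abstract repeats it. Neither place names city as a factor, covariate or stratum for any outcome, and neither says that city will be left out. City is recorded on the demographic questionnaire, so the variable will be available.

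**The concern.** Blocking within city makes the two arms nearly equal in their mix of cities. Differences between cities therefore add almost nothing to the sampling variation of the treatment contrast. An analysis without city still counts those differences as residual variation between couples, so it reports a standard error larger than the true one. Confidence intervals are then too wide, p-values too large, and part of the precision that the stratification bought goes unused.

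This matters only so far as city is related to outcome. The protocol article chose cities with a wide geographical spread for generalisability and names socioeconomic status as a potential confounder when it discusses centres. That makes some city differences plausible, but the article gives no figure for them.

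**Working it through.** **Inputs.** From the Sample size section: "small standardized Cohen effect size" of 0.2, a "type I error of 5"%, power of 90%, 527 per group, and "considering 15% of loss to follow up". From the Randomization section: five strata and blocks of 4. Assumed, because the documents do not give it: the share R of the variance of the tested outcome that lies between cities, taken as 2%, 5% and 10%.

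**The plan's own figure.** A two-sided two-sample t-test with d = 0.2, alpha 0.05 and 90% power needs 527 per group by the noncentral t (526 by the normal approximation; a one-sided test would need 429). Then 527 / 0.85 = 620 per group. Both stated figures reproduce, so 527 evaluable couples per group is the base for what follows.

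**Effect of leaving city out, comparison at one time point.** Take total variance as 1. With allocation balanced within city, the true variance of the group difference is (1 − R) times the variance that a city-free analysis estimates. Write r = 1/√(1 − R).

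- Reported SE / true SE = r.
- Actual two-sided alpha = 2 × [1 − Φ(1.96 r)].
- Noncentrality at R = 0: 0.2 × √(527/2) = 3.247.
- Power without city ≈ Φ[(3.247 − 1.96) r].
- Power with city ≈ Φ[3.247 r − 1.96].

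Example at R = 5%: r = 1/√0.95 = 1.026. Alpha = 2 × [1 − Φ(2.011)] = 4.4%. Without city, Φ(1.320) = 90.7%; with city, Φ(1.371) = 91.5%. The noncentral t gives 90.6% and 91.4%. The table uses the noncentral t for power.

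| Assumed city share R | SE too large by | Actual alpha | Power without city | Power with city | Gain (points) |
|---|---|---|---|---|---|
| 0% | 0% | 5.0% | 90.0% | 90.0% | 0 |
| 2% | 1.0% | 4.8% | 90.3% | 90.6% | 0.3 |
| 5% | 2.6% | 4.4% | 90.6% | 91.4% | 0.8 |
| 10% | 5.4% | 3.9% | 91.2% | 92.8% | 1.6 |

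Power without city is not fixed at 90.0%. The stratified allocation already narrows the true spread of the estimate, so the unadjusted test gains a little as well.

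**Simulation check.** City sizes were 440/200/200/200/200, with blocks of 4, 15% random loss, one time point and R = 10%. Type I error was 3.8% without city and 4.8% with it. Mean reported SE was 0.0616 against 0.0585, a ratio of 1.05.

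**The repeated measures ANOVA itself.** It contains two tests of the group effect, and they behave differently.

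- *Group main effect.* This compares couple averages over the visits against between-couple error. City variance stays in that error, so the argument above applies.
- *Group by time.* This uses changes within couples. A city difference that is constant over visits cancels from both the contrast and its error term.

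A simulation with four visits, a stable city effect worth 10% of variance and city omitted gave type I error of 3.5% for the group main effect and 5.2% (nominal) for group by time.

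**Planned pregnancy and other binary outcomes.** These are also between-couple comparisons, so the direction is the same for a difference in proportions. No separate figure was computed for them.

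**The case against.** The strongest objection is that this is silence, not exclusion. The outcome sentence names a family of methods and lists no model terms. Stratification factors are often specified in a full protocol or SAP, and neither is shown here. A reader might infer that the investigators have decided to ignore city; the article does not say that. What remains is that the method as stated does not carry the stratification into the analysis, and that section is otherwise specific about tests, software and significance level. Asking for city to be added, or for confirmation that it is already there, is therefore fair. Calling it an error in the plan would not be.

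A second objection is that group by time is the natural test in a pre-test/post-test design, and that test is largely immune to stable city differences. This stands in full and limits the point to between-couple comparisons. It does not remove the point. The article does not say which term is decisive, the sample size rests on a 3-month comparison of two groups, and planned pregnancy has no baseline value to difference against.

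Third, a reader might infer larger power gains of 0.6, 1.4 and 2.8 points by measuring the adjusted analysis against 90.0%. That double counts, because stratification has already raised the power of the unadjusted test.

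**Conclusion.** The point holds as a minor one. Randomisation is stratified by city and the stated outcome analysis names no city term. If city is related to outcome, between-couple comparisons will be somewhat conservative: for an assumed city share of 2% to 10%, the SE is 1.0% to 5.4% too large, actual alpha is 4.8% to 3.9%, and 0.3 to 1.6 points of power are forgone. If city is unrelated to outcome, nothing is lost.

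Two stronger readings are tempting and unsupported. One is that false-positive risk is inflated: the error runs the other way. The other is that the trial becomes underpowered: under the plan's own d = 0.2 and 527 evaluable couples per group, power stays above 90% with or without city whenever city carries any variance, and equals the planned figure when it carries none. Nor can standard errors be said to mismatch the design for every test, since group by time is nominal when city effects are stable.

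The sizes rest on the assumed range for R, on loss unrelated to arm and city, and on a single-time-point calculation for a quantitative outcome.

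**What to change.** Add one sentence to the Statistical method section: city (five levels) enters as a fixed factor in each between-group outcome model, and as a stratum or covariate in the analysis of planned pregnancy and the other binary outcomes. If the SAP already says this, a line confirming it is enough.

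The cost is four degrees of freedom per model, which is negligible with about 200 to 440 couples per city, and no new data. Sample size and randomisation do not change. Including city also gives some protection if loss to follow-up disturbs the balance between arms within cities.

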### Data collection

Data will be collected by questionnaires at baseline and 3, 12 and 18 months after the intervention in each selected city (Table 1). The post-test questionnaires will be completed by the participants through online forms. The participants’ phone number, email address and social network’s ID (WhatsApp) will be asked in order to send the post-test questionnaire links and some virtual educational materials.

In each city, two research collaborators will cooperate with the principal investigator. They will be introduced by the Ministry of Health and Medical Education, associated office for premarital counselling courses in all provinces. We will have a training session for these research staff and they will be justified about the study aims and procedure of data collection as well as educational intervention. They need to be in close contract with the principal investigator.

To minimize loss to follow up, we will provide an incentive to the eligible participants (A gift voucher for free sexual and reproductive health counselling) on the completion of the survey which may increase response rates. Four reminder emails or text messages will send out to non-respondents at one, two, three, and 4 weeks; a fifth telephone reminder was also undertaken.

Since a recent study in Iran showed an average interval between marriage and first pregnancy as about 15.4 ± 0.2 months in Iran [24], we are planning to follow the participants for occurrence of planned pregnancy about 18 months after the intervention.

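### Repeated measures ANOVA in SPSS by default drops anyone who misses one of the four waves, so the knowledge and intention scores are compared among completers; a mixed model would use all observed waves

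*Protocol article*

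**What the plan says.** The protocol article's Statistical method section assigns the chi-square or Fisher test, the t-test and the Mann–Whitney test to the comparison of groups at baseline. For outcomes it names one method: "To compare the outcomes between the two groups over the time, repeated measures ANOVA will be used". The software is also fixed: "Data will be analyzed using the SPSS software version 22". The abstract repeats the ANOVA.

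The Data collection section sets four waves: "Data will be collected by questionnaires at baseline and 3, 12 and 18 months after the intervention in each selected city". Follow-up is remote: "The post-test questionnaires will be completed by the participants through online forms". Non-response is foreseen, with an incentive, a telephone reminder and written reminders: "Four reminder emails or text messages will send out to non-respondents at one, two, three, and 4 weeks".

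The Sample size section bases the main calculation on knowledge and intention at 3 months (d = 0.2, 5% type I error, 90% power, 527 per group). It then allows for attrition once: "considering 15% of loss to follow up, the sample size was calculated 620 couples in each group using the G-Power software". A second calculation gives 660 couples in total, 330 per group, for the repeated measures ANOVA over all four time points.

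**The concern.** The standard repeated measures ANOVA procedure in SPSS needs a complete row of measurements. By default a participant with one missing wave is removed from the whole analysis, including from waves that they did answer. With three online follow-ups over 18 months, the people who answer all of them are a smaller and possibly different group from those who answer at month 3.

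Two things are at stake. The first is precision at 3 months: the 527 per group was worked out for a comparison that needs only the 3-month form, whereas the stated analysis needs all four. The second is the comparison itself. Participants are not blinded, and only one arm receives the additional four-week training. If staying to the last wave depends on arm and on earlier scores, a contrast among completers no longer estimates the difference between the groups as randomised, even at month 3.

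**Working it through.** **Inputs.** From Sample size: d = 0.2, alpha 0.05, power 90%, 527 evaluable and 620 recruited couples per group, 15% loss stated once, and 330 per group for the ANOVA. From Data collection: three follow-up waves. Not given in the article: whether the test is two-sided, how the 15% divides between waves, and the correlation between waves.

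**1. Reproducing the plan's figures.**
- Two-sample t-test, d = 0.2, alpha 0.05, power 90%: the two-sided calculation gives 527 per group (noncentral t). A one-sided test would need about 429, so two-sided is the reading that fits.
- Attrition: 527 / (1 − 0.15) = 620.
- ANOVA: the between-groups test with f = 0.1, four measurements and an assumed correlation of 0.5 has noncentrality N × f² × 4 / (1 + 3 × 0.5). It reaches 90% power at N = 660 in total. The stated figure is reproduced under that assumption.

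**2. Complete cases per group, by reading of the 15%.**
- Total loss by month 18, or the same people missing each time: 620 × 0.85 = 527 (15% removed).
- 15% missed independently at each of three waves: 620 × 0.85³ = 620 × 0.614 = 381 (39% removed).
- 15% missed at each wave, never by the same people: 620 × (1 − 0.45) = 341 (45% removed).
- Lower rates, independent by wave: 5% removes 1 − 0.95³ = 14%, and 10% removes 1 − 0.90³ = 27%.

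**3. Power for d = 0.2 at month 3 on those complete cases (two-sided t-test).**
- 527 per group: 90%.
- 381 per group: 79%.
- 341 per group: 74%.

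If 15% miss the month-3 form, an analysis that uses every observed month-3 score keeps about 527 per group for that contrast, whatever happens later.

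**4. Power for the ANOVA's between-groups test, averaged over time (f = 0.1).**
- Correlation 0.5: 94% with 762 couples in total (381 per group) and 91% with 682 (341 per group).
- With 762 couples: 91% at correlation 0.6 and 88% at 0.7.
- Threshold: 1 − 330/620 = 47% of couples could be incomplete before the number falls below the plan's own 330 per group.

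**5. Possible bias (simulation; every dropout input is an assumption).** 620 per group, correlation 0.5 between waves, and a true difference of 0.20 SD at each follow-up. About 24% drop out after month 3 in each arm. In the trained arm, lower month-3 scorers drop out more, with log-odds 0.25 to 0.5 per SD.
- Completers, month 3: average difference about 0.26 to 0.32.
- Completers, month 18: about 0.23 to 0.26.
- Estimate using all observed scores, month 18: about 0.20.
- With dropout unrelated to scores, completers also average 0.20, and only precision is lost.

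**The case against.** **The plan sizes this very analysis.** It asks for 330 per group for the ANOVA, and every scenario above leaves more than that. A reader might infer that the trial is underpowered for its stated analysis. The documents do not support this. The loss of power concerns the 3-month contrast on complete cases, not the time-averaged test.

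**The size of the loss is not a document figure.** A reader might take 39% as the expected loss or as a ceiling. It is neither. It applies the single 15% to each wave and assumes independence, within a range of 15% to 45%. Independence is doubtful too, since people who miss one online form tend to miss others. The planned incentive and reminders may keep losses low.

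**The bias is assumed.** Nothing in the article supports the direction or strength of the simulated dropout. The all-data estimate recovers 0.20 because dropout was generated from observed scores, which is the condition that such a model needs. This stands: bias is possible, not shown.

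**Missing-data handling may be in the full protocol or SAP.** Imputation before the ANOVA is not excluded, and silence on it is no fault in an article. But the method and software are stated here, and their default is to discard incomplete rows. The abstract also lists t-tests without limiting them to baseline; the Statistical method section does limit them.

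**The unit is unclear.** The figures above count couples. If both partners' scores are analysed, the 39% scenario leaves about 762 people per group. Divided by the stated design effect of 1.5, that is 508 effective, with about 89% power at 3 months. This stands as a reason to treat 79% as one scenario and to allow for correlation between partners.

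**Conclusion.** The concern holds as a weakness of a method that the article states. Repeated measures ANOVA in SPSS 22 by default compares completers and discards month-3 scores from anyone who misses another wave. Counting couples, complete cases run from 527 to 341 per group, depending on how the 15% is read, and power for d = 0.2 at month 3 runs from 90% to 74% (79% under independence). The ANOVA's own requirement of 330 per group is met throughout.

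Bias is conditional. It needs later response to depend on arm and scores, which is plausible in an unblinded trial with online follow-up but is not established by the documents. The point covers the quantitative scores: knowledge and the scaled intention items. Planned pregnancy is binary and raises a separate question. Recruitment need not change, and a better analysis of the same data is available at little cost.

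**What to change.** In the Statistical method section and the abstract, replace repeated measures ANOVA for the quantitative scores with a linear mixed model for repeated measures, available as MIXED in SPSS 22:

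- Include every randomised participant with at least one observed wave.
- Fit arm, wave and arm-by-wave terms, with an unstructured covariance across waves. This also removes reliance on sphericity, a secondary gain.
- Add a couple-level random effect if both partners' scores are analysed.
- Report the 3-month difference with its 95% confidence interval from this model.
- Keep the complete-case ANOVA as a sensitivity analysis.

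The model is valid when missingness depends on arm and on scores already observed. It does not protect against dropout that depends on unobserved scores.

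Cost: a change of wording and slightly more analysis work. No new data, contacts or participants are needed. It should be settled before any unblinded analysis.

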### Outcomes

The primary outcomes are fertility knowledge, childbearing intention and the first planned pregnancy rate (positive pregnancy test).

The secondary outcomes include the contraception method use, miscarriage and unplanned pregnancy.

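### Three unranked primary outcomes share a general 0.05 threshold with no success rule: about 14% family-wise error if any one counts and each is tested once

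*Protocol article*

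**What the plan says.** The Outcomes section of the protocol article states: "The primary outcomes are fertility knowledge, childbearing intention and the first planned pregnancy rate (positive pregnancy test"). The Abstract and Table 1 list the same three, and none is placed above the others.

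The Statistical method section gives one significance rule covering all analyses: a P "value < 0·05 will be considered statistically significant". It names repeated measures ANOVA for comparing the groups over time. It gives no testing order and no adjustment.

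The Sample size section works "with a type I error of 5% (α = 0.05"), undivided. It bases the calculation on "fertility knowledge and intention toward childbearing that are important to be measured 3 months after the intervention". Planned pregnancy has no assumed control rate, target difference or power in that section.

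**The concern.** With three primary outcomes, the plan has to say what makes the trial positive: any one outcome, all of them, or a stated order. This document does not say, and it allows each outcome the full 0.05. A reader is then free to call the intervention effective on whichever outcome crosses the threshold, and the error rate of that claim is above 5%.

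This matters because the Discussion section links a finding of effectiveness to government policy and to adding the education to premarital courses. There is a second, smaller risk: a non-significant result on planned pregnancy could be taken as evidence of no effect, although that outcome did not drive the sample size.

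**Working it through.** **Inputs.**
- Three primary outcomes (Outcomes).
- Threshold 0.05 for all analyses (Statistical method) and undivided alpha 0.05 (Sample size).
- "a small standardized Cohen effect size (d = 0.2"), and "a type II error of 10% (β = 0.1; power = 90"%) (Sample size).
- "sample size obtained 527 in each group", raised to 620 for 15% loss to follow-up (Sample size).
- Correlations between test statistics: not in the document. I assume 0.3, 0.5 and 0.8.

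**Step 1: reproduce the plan's own figure.** n per group = 2(z₀.₉₇₅ + z₀.₉₀)²/d² = 2(1.960 + 1.282)²/0.04, which rounds up to 526. The exact t calculation gives 527, as stated. A one-sided test would give 429, so the plan's alpha is two-sided 0.05. Then 527/0.85 = 620. The stated size is therefore that of a single test at the full 0.05, with nothing set aside for further outcomes.

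**Step 2: chance of at least one false-positive primary result**, with one test per outcome and any one success counting.
- Independent tests: 1 − 0.95³ = 1 − 0.8574 = 14.3%.
- Upper bound under any dependence: 3 × 0.05 = 15%.
- Two-sided z tests with a common correlation (simulation, 2,000,000 draws): 13.6% at 0.3, 12.5% at 0.5, 9.8% at 0.8.

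At the strongest correlation tried, the rate is still about twice 5%.

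**Step 3: more than one test per outcome.** Table 1 has each outcome measured at 3, 12 and 18 months. A repeated measures ANOVA yields both a group term and a group-by-time term. The section on the childbearing intention questionnaire describes several parts with different response formats and names no single score. If more than one of these is tested per outcome, the rate exceeds the Step 2 figures. The document does not fix how many tests there will be, so I put no number on this.

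**Step 4: what control would cost in power**, for d = 0.2 with 527 evaluable couples per group. The noncentrality is 0.2 × √(527/2) = 3.247.
- At alpha 0.05: Φ(3.247 − 1.960) = 90.1%; exact t 90.0%.
- At alpha 0.05/3 = 0.0167: Φ(3.247 − 2.394) = 80.3%; exact t 80.2%.
- Three independent tests at 0.0167 have a family-wise error of 1 − (1 − 0.0167)³ = 4.9%.
- Keeping 90% power at 0.0167 would need 676 per group, or 676/0.85 = 796 after loss to follow-up, against 620 planned.

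In a fixed sequence the first test keeps 90%. If the second outcome also has d = 0.2, the chance of passing both is 0.90 × 0.90 = 81% when independent, and at least 1 − 0.10 − 0.10 = 80%. Under Holm, any outcome with p below 0.0167 is rejected whatever happens to the others, so 80% is a floor for each outcome with d = 0.2.

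**The case against.** The strongest reply is that this is a condensed article, its analysis plan is not shown, and multiplicity procedures are often placed there. On that view the threshold sentence is a routine line. It does not say that one significant outcome makes the trial positive, and if all three had to succeed there would be no inflation. Part of this stands: the 14% needs an any-one-counts rule that the document does not state. But the article is not silent on significance. It fixes 0.05 for all analyses and sizes the trial at that undivided alpha, so an analysis plan that added a procedure would have to depart from it. An all-must-succeed reading also fits poorly with a sample size that leaves out one of the three.

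One could also argue that the Sample size section marks knowledge and intention as the main pair ("According to our primary outcomes including fertility knowledge and intention toward childbearing"). That is a planning choice and not a testing order, and two independent tests at 0.05 would still give 1 − 0.95² = 9.75%.

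Some stronger readings are tempting but unsupported:
- That 14% is a ceiling for the trial. It applies to one test per outcome only.
- That 34 intention items (2 + 7 + 8 + 4 + 13) will be tested. Those counts describe the source instrument. The protocol says only parts of it will be used and that questions may be revised.
- That the trial is underpowered for planned pregnancy. With no control rate or target difference stated, this cannot be concluded, and power does not affect the false-positive rate.
- That the protocol implies an order. The Background section calls planned pregnancy a long-term goal and the Sample size section looks to month 3 for the other two, but nothing ranks knowledge above intention.

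**Conclusion.** The concern holds in a conditional form. The document applies 0.05 to three unranked primary outcomes without a success rule. If any one success counts and each outcome has one test, the family-wise false-positive rate is about 14% (15% at most; about 10% to 14% at assumed correlations of 0.8 to 0.3). More tests per outcome would raise it; requiring all three to succeed would remove the inflation.

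The power figures take 527 independent evaluable couples per group at face value. The Sample size section also mentions a design effect of 1.5, which is not visible in 620 = 527/0.85. If it were real, the effective size would be 527/1.5 = 351 per group, with power of about 75.5% at 0.05 and 60.1% at 0.0167. That is a separate matter.

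This should be corrected, but it does not undermine the design.

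**What to change.** 1. Name one test per primary outcome: Cardiff scale score at month 3, one named intention measure at month 3, and planned pregnancy by month 18. Treat other time points, model terms and items as supportive.
2. For these three tests, replace the general 0.05 with a procedure fixed in advance that holds family-wise error at 5%. Two options are reasonable:
   - *Fixed sequence*: knowledge, then intention, then planned pregnancy, each at two-sided 0.05 only if the one before is significant. It keeps the planned 90% for the first test and fits the Background and Sample size sections, but allows no confirmatory claim after a failure. A null on intention would close off planned pregnancy.
   - *Holm*: no gate between outcomes, so pregnancy does not depend on intention. The price is a first step at 0.0167, with about 80% power for d = 0.2 at 527 per group.
3. Report all three with confidence intervals whatever the test results. State that the sample size rests on knowledge and intention, so that a null on planned pregnancy is not read as no effect.

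The cost is a few sentences and no extra couples. The choice between the two options belongs to the investigators and should be made before outcome data are seen.
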